### Exclusion criteria

Cancer, diabetes, coagulation diseases, anemia; orthodontic treatment; pregnant women or lactating women and the impossibility to use the rubber dam isolation technique.

### Ethics and dissemination

The study will be conducted in accordance with Decree 158/19 of the Executive Branch, which regulates research involving human subjects in Uruguay. Additionally, the study will comply with Law 18,331 (Law on the Protection of Personal Data and the Action of "Habeas Data").

The Research Ethics Committee of Universidad Católica del Uruguay approved the protocol (211103b). Additionally, the protocol was registered under number NCT06413836 in the Clinical Trial Protocol Registration and Results System. The results from this trial will be presented at conferences and published upon completion of the study.

The study is anticipated to last up to 20 months, beginning from the recruitment date. The protocol was developed in accordance with the SPIRIT guidelines (Standard Protocol Items: Recommendations for Interventional Trials) (Fig 1), and the SPIRIT checklist is provided as an additional file. Upon completion of the study, the CONSORT guidelines (Consolidated Standards of Reporting Trials) will be adhered to for reporting.

**Fig 1 pone.0315169.g001:**
[figure not shown]
SPIRIT figure recommended by 2013 SPIRIT statement.

Recruitment will commence following the acceptance of the protocol for publication.

Participants will be informed that they may withdraw from the study at any time and for any reason if they choose to do so. Researchers may also remove participants from the study if deemed necessary.

### Sample size calculation

The sample size calculation was conducted with the statistical software G-Power 3.1 (Universität Kiel, Germany) applying the chi-square homogeneity test. Identical sample sizes were determined for both the aPDT group and the sham group. A type I error rate of 5% and a statistical power of 80% were specified [15], resulting in a required sample size of n = 70, accounting for a 10% loss to follow-up. The sample size calculation was based on established literature, and a significance level of 5% will be employed [8, 13, 16].

### Randomization

Participants will be selected and randomly assigned to one of two experimental groups. Randomization will be carried out by an investigator who is not directly involved in participant treatment, using the website www.randomizer.org. The randomization results will be communicated through opaque, sealed envelopes containing information about whether the treatment is laser-based or conventional. These envelopes will be securely stored and will not be accessible to the observing researcher. Prior to treatment, the operator responsible for administering the therapy will receive the envelope to determine the assigned treatment group.

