## Materials and methods

### Study design

This study will be a two-arm, single-center, double-blind, randomized controlled clinical trial with a 1:1 allocation ratio. Upon approval of the study protocol by the Research Ethics Committee of the Universidad Catolica del Uruguay—UCU, the trial will be conducted involving participants with apical periodontitis and a fistula in single-rooted teeth. Inclusion criteria require initial periapical radiography demonstrating apical radiolucency and fistulography to confirm the presence of the fistula. Recruitment will occur at the University Health Clinic of UCU, where the study will be conducted. Participants will be required to read, understand, and sign the Free and Informed Consent Form, which has been approved by the Research Ethics Committee. (211103b).

All participants will receive treatment from a single experienced clinician, who will oversee data collection and procedural execution. Initial periapical radiographs will be required for all participants. Root canal preparation will be conducted using a rotary endodontic device (DENTSPLY). A diode laser apparatus (DMC, THERAPY EC, Sao Carlos, Brazil) with a wavelength of 660 nm, power output of 100 mW, and an irradiation duration of 3 minutes will be utilized [14].

Participants and outcome evaluators will remain blinded to the assigned interventions throughout the study. Unblinding will be permitted only under exceptional circumstances where knowledge of the actual treatment is critical for the ongoing management of the participants.

All participants will receive conventional treatment as described below. Additionally, the study group will undergo antimicrobial photodynamic therapy (aPDT), while the control group will receive a simulation of the laser application. During this process, both participants and the operator will be required to wear protective eyewear.

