### Interventions

All participants will be treated by the same experienced endodontist, who will oversee both data collection and procedural management. Each participant will receive conventional treatment.

A baseline periapical radiograph will be required for all participants, as well as follow-up radiographs at 15- and 30-days post-treatment. These radiographs will be obtained by a different operator, who will analyze them. This operator will be blinded to the intervention received by each participant.

Conventional treatment will be performed using the Protaper rotary system (Dentsply Maillefer rotary instruments). The canal irrigation will be with 5% sodium hypochlorite, 17% ethylenediaminetetracetic acid, and 2% chlorhexidine [14]. Subsequently, a methylene blue solution in a surfactant medium will be applied using a size 30 paper point cone (Dentsply), with a pre-irradiation time of 1 minute. The study group will receive a 3-minute irradiation period, while the control group will be administered the photosensitizer along with a simulated laser application. This simulation will be achieved by placing an aluminum foil barrier at the tip of the laser equipment to block the light. During these procedures, both the operator and participants will wear protective eyewear to ensure eye safety and concealment. Calcium hydroxide will be applied to the root canals as a long-term intracanal dressing for endodontic treatment.

A diode laser device (Therapy EC, DMC, São Carlos, Brazil) with a wavelength of 660 nm and a power output of 100 mW will be used, according to the parameters detailed in Table 1. The pre-irradiation and irradiation durations will be identical for both groups.

**Table 1 pone.0315169.t001:** Dosimetric parameters.

PARAMETERS	
Wavelength (nm)	660
Operating mode	Continuos
Power (mW)	100
Irradiance (mW/cm^2^)	250
Target irradiated area (cm^2^)	0.4
Exposure time (s)	180
Radiant exposure (J/cm^2^)	10
Energy (J) per point	18
Number of irradiated points	2
Application technique	Entry duct and fistula
Number of sessions	1

The photosensitizer used will be methylene blue at a concentration of 0.005%, dissolved in 0.25% sodium dodecyl sulfate.

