### Blinding

Participants and outcome evaluators will be blinded to the assigned interventions. Unblinding will be permitted only under exceptional circumstances where knowledge of the actual treatment is crucial for the continued management of the participants.

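### The sole operator learns the arm before treatment begins, although the arms differ only at irradiation, so canal preparation and irrigation are needlessly done unblinded

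*Protocol article*

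**What the plan says.** **When the arm is revealed.** Under Randomization, allocation is held in "opaque, sealed envelopes containing information about whether the treatment is laser-based or conventional". The sentence before the key one keeps these envelopes from an observing researcher. Then: "Prior to treatment, the operator responsible for administering the therapy will receive the envelope to determine the assigned treatment group".

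**Who treats.** Study design: "All participants will receive treatment from a single experienced clinician, who will oversee data collection and procedural execution". Interventions repeats this: "All participants will be treated by the same experienced endodontist, who will oversee both data collection and procedural management".

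**Order of steps.** Interventions describes rotary preparation and irrigation, and then: "Subsequently, a methylene blue solution in a surfactant medium will be applied using a size 30 paper point cone (Dentsply"). A 1-minute pre-irradiation time follows. The study group is then irradiated for 3 minutes, while controls receive the same photosensitizer and a simulated application. Of the sham it says: "This simulation will be achieved by placing an aluminum foil barrier at the tip of the laser equipment to block the light". Pre-irradiation and irradiation times are the same in both groups. A calcium hydroxide dressing is listed last.

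**Who is blinded.** The Blinding section states: "Participants and outcome evaluators will be blinded to the assigned interventions". Study design says the same and calls the trial double-blind. Interventions assigns the baseline, 15-day and 30-day radiographs to a different operator, who is blinded and also reads them. Under Primary outcomes, fistula resolution is judged from clinical examination together with radiographs. The clinical examiner is not named.

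**The concern.** Shaping and irrigation depend on the operator, and they plausibly affect whether a fistula closes. If the operator knows the arm while doing them, care or thoroughness can differ between arms, even without intent. The trial would then compare light plus one standard of preparation with sham plus another. A blinded examiner would record that difference faithfully, so blinding of evaluators gives no protection against it.

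The exposure is avoidable, because nothing before irradiation requires the allocation.

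There is a smaller issue alongside it. The one person certain to know the arm also oversees data collection, and the article does not say how this fits with blinded evaluation of a clinically judged primary outcome.

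**Working it through.** The plan has no figure to reproduce on this point, so the main check sets the sections side by side.

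**Step 1: which steps need the allocation?**

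| Step (Interventions) | Differs by arm? | Operator knows the arm under the present rule? |
|---|---|---|
| Rotary preparation | No | Yes, on the natural reading |
| Irrigation | No | Yes, on the natural reading |
| Photosensitizer placement | No | Yes |
| 1-minute pre-irradiation | No | Yes |
| 3 minutes of light or foil-blocked light | **Yes** | Yes |
| Calcium hydroxide dressing | No | Yes |

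Only one row needs the allocation. The Abstract is looser: it describes Group I as conventional treatment only and counts the photosensitizer as part of aPDT. Read that way, the arms would separate one step earlier, but preparation and irrigation would still be common to both. The point about those two steps holds on either reading.

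**Step 2: does the envelope rule cover preparation?** The wording is that the operator gets the envelope before treatment. The envelope's content distinguishes two whole treatments, laser-based or conventional, and conventional treatment begins with canal preparation. Receipt before preparation is thus the natural reading, but it is an inference.

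**Step 3: what would later opening protect?** It would keep rows 1 to 4 blinded. An operator who handles the laser sees the foil, so rows 5 and 6 stay unblinded.

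**Step 4: data collection.** Study design and Interventions give the treating clinician oversight of data collection. Study design and Blinding say evaluators are blinded. A separate blinded person is identified by task only for the radiographs. The observing researcher is kept from the envelopes, but that role is not defined or linked to the fistula examination. These statements can be compatible. The article does not say how.

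**Step 5: can it be sized?** Not from the documents, which give neither resolution rates nor an effect size. The following is purely hypothetical. Take 70 per group with 10% loss, so 70 × 0.90 = 63 evaluable per arm, and assume the light has no true effect. Suppose something other than the light moves the aPDT arm's resolution rate from p to q. The chance of a significant result favouring aPDT (two-sided 5%) is

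Φ[ ((q − p) − 1.96·√(2·p̄(1 − p̄)/63)) / √((p(1 − p) + q(1 − q))/63) ], where p̄ = (p + q)/2.

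For p = 0.60 and q = 0.64: p̄ = 0.62, the null standard error is 0.0865 and the alternative standard error is 0.0864. This gives Φ[(0.04 − 0.1695)/0.0864] = Φ(−1.50) = 0.067.

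| Assumed p | q if 10% of failures become successes | Chance | q if 20% do | Chance |
|---|---|---|---|---|
| 0.50 | 0.55 | 8.1% | 0.60 | 20.2% |
| 0.60 | 0.64 | 6.7% | 0.68 | 15.2% |
| 0.70 | 0.73 | 5.6% | 0.76 | 11.4% |
| 0.80 | 0.82 | 4.7% | 0.84 | 8.4% |

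The nominal chance in that direction is 2.5%. Every p and q here is an assumption. The table shows only how sensitive the test is to a spurious gap, not that one will occur.

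**The case against.** Several points on the other side have force.

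- **The rule says before treatment, not before canal preparation.** This is true. A reader could take treatment to mean the laser step. That is the less natural reading, and if it is what the authors intend, the fix only makes it explicit.
- **An operator who handles the foil cannot be blinded anyway.** This stands for irradiation and the dressing. It does not justify revealing the arm for the earlier steps. The protective eyewear, which the article says also serves concealment, does not help once the operator has read the envelope.
- **A reader might infer that the endodontist scores fistula closure, so that the primary outcome is assessed unblinded.** The article does not support this. Overseeing data collection is not examining or scoring. Evaluators are stated to be blinded, radiographs go to a different blinded operator, and the observing researcher cannot reach the envelopes. What remains is an unnamed examiner and an unreconciled oversight role. Part of this may be settled in a fuller protocol that is not shown.
- **A reader might call the double-blind label false.** It is not, on the article's own terms: participants and evaluators are the blinded parties, and operator blinding is never claimed. The label is merely imprecise.
- **A reader might assume that bias would favour aPDT.** The Introduction states a hypothesis of equal efficacy, and an operator might equally take more care with controls. The direction is unknown.
- **A reader might take inflated false-positive rates as the size of the problem.** They rest on assumed rates without a source. If attributed to miscalled fistulas, they also require an unblinded assessor, which the plan's own statements exclude.

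**Conclusion.** The main point holds as an avoidable weakness of design. One operator treats everyone, is told the arm before treatment, and performs operator-dependent co-treatment that is meant to be identical in both arms. This rests on two things: the stated order of steps, and the natural but not literal reading that treatment includes canal preparation. Size and direction cannot be established, and the figures in the working table are hypothetical.

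The secondary point is a request to reconcile, not a proven breach. The operator's oversight of data collection and the blinding of evaluators need a sentence to connect them, because the clinical fistula examiner is not named.

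**What to change.** 1. **Randomization section.** State that the envelope is opened only once canal preparation, irrigation and photosensitizer placement are complete, immediately before irradiation. Cost: one sentence and a brief pause mid-procedure. Limit: the dressing placed after irradiation stays unblinded if the same operator handles the laser, and the article should say so.
2. **Interventions, Blinding and Primary outcomes sections.** State that the blinded operator who already takes the 15- and 30-day radiographs also makes and records the fistula examination at those visits, and that the endodontist's oversight excludes outcome data. Cost: one or two sentences and a short added task for a person already in the plan. No extra visits or participants are needed.
3. **Study design section.** Beside the double-blind label, say that the treating operator is not blinded, and from which step.

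The article places the start of recruitment after acceptance for publication, so on its own terms these changes can precede enrolment. If enrolment has begun, record the date of the change.

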### Blinding

Participants and outcome evaluators will be blinded to the assigned interventions. Unblinding will be permitted only under exceptional circumstances where knowledge of the actual treatment is crucial for the continued management of the participants.

## Outcome variables

### Primary outcomes

• Resolution of the Fistula: The primary outcome will be the resolution of the fistula, assessed at 15- and 30-days post-treatment. This will be evaluated based on clinical examination and radiographic evidence.

• Radiographic Improvement: The improvement in radiographic signs of apical periodontitis will be assessed at 15- and 30-days post-treatment, focusing on changes in the periapical radiolucency.

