**Methods:**

The study will involve 140 teeth with apical periodontitis and fistulas. The teeth will be randomly assigned to one of two treatment groups. Group I will receive only the conventional endodontic treatment, which includes root canal cleaning, shaping, and obturation. Group II will undergo the same conventional endodontic treatment, but with an additional step of aPDT. The aPDT procedure involves applying a photosensitizer to the root canal and irradiating it with light to produce reactive oxygen species. Each group will consist of 70 teeth to ensure adequate statistical power. The primary outcome is fistula resolution, assessed clinically at 15 and 30 days post-treatment. The secondary outcome is the comparison of apical radiolucency from periapical radiographs to evaluate healing and reduction of periapical pathology.

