Thus, the aim of this protocol is to evaluate the photodynamic effect of methylene blue in 0.25% SDS for the treatment of apical periodontitis in presence of fistula. The hypothesis to be tested is that both interventions will exhibit equivalent efficacy, with no statistically significant difference. The evaluation will focus on the resolution of the fistula and the improvement of radiographic indicators, assessed at 15 and 30 days post-endodontic treatment for apical periodontitis [13].

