### Statistical analysis

The distribution of data within each group will be checked. The categorical variables will be analyzed using the Pearson Chi-square test or two sample t-test. The correlation between clinical or radiographic findings and the healing fistula will be analyzed by Pearson Chi-square test or Mann Whitney U test [13].

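### Fistula resolution is primary at both day 15 and day 30 with no decisive visit or combination rule, so the stated 5% level and 80% power cannot both be tied to one primary test

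*Protocol article*

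**What the plan says.** Three places in the Protocol article give the timing of fistula resolution, and each gives two visits.

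- Abstract, Methods: "The primary outcome is fistula resolution, assessed clinically at 15 and 30 days post-treatment".
- Introduction, closing paragraph with the hypothesis: fistula resolution and radiographic indicators are both "assessed at 15 and 30 days post-endodontic treatment for apical periodontitis".
- Outcome variables, Primary outcomes: "The primary outcome will be the resolution of the fistula, assessed at 15- and 30-days post-treatment".

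The sample size section works with a single test. It names the chi-square homogeneity test and says "A type I error rate of 5% and a statistical power of 80% were specified", "resulting in a required sample size of n = 70, accounting for a 10% loss to follow-up", and that "a significance level of 5% will be employed". The Abstract shows that 70 is the number per group. No effect size or closure rate is given.

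The Statistical analysis section says "The categorical variables will be analyzed using the Pearson Chi-square test or two sample t-test" and ties the test to no visit.

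The Primary outcomes section also lists a second item: "The improvement in radiographic signs of apical periodontitis will be assessed at 15- and 30-days post-treatment". The Abstract instead makes apical radiolucency the secondary outcome.

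**The concern.** A Pearson chi-square test compares two groups on one classification. Fistula closed or not, at two visits, gives two such tests unless a rule says otherwise. The protocol has three natural readings:

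- **Either visit counts.** The 5% level does not hold for the primary claim.
- **Both visits must be significant.** The 5% level is safe, but the 80% power does not hold for the primary claim.
- **One visit decides.** Both figures can hold, but the protocol does not say which visit it is.

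The visit, or the rule, could then be chosen after the data are seen. A difference at day 15 that has gone by day 30 could be reported as a success or as a failure, and the protocol would not contradict either report.

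**Working it through.** **Inputs from the protocol.** Level 5%, power 80%, 70 teeth per group, 10% loss, 1:1 allocation, Pearson chi-square.

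**Inputs assumed.** Closure rates at each visit, and that a fistula closed at day 15 is still closed at day 30. The protocol gives neither.

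**The plan's own figure.** Evaluable teeth per group: 70 × 0.90 = 63. The 63 cannot be derived, because no effect size is stated. It is attainable: with an assumed w = 0.25, total N = (1.96 + 0.84)² / 0.25² ≈ 126, which is 63 per group, and 63 / 0.90 = 70. That is the size for one 1-df test at 5%, with nothing set aside for a second test.

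**If either visit counts: theory.** For two independent tests the rate is 1 − 0.95² = 9.75%. The visits are correlated, which lowers it. For two two-sided 5% tests under a bivariate normal:

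| Correlation | 0 | 0.3 | 0.5 | 0.7 | 0.8 | 0.9 | 0.95 | 1 |
|---|---|---|---|---|---|---|---|---|
| Rate | 9.75% | 9.5% | 9.1% | 8.4% | 7.8% | 7.0% | 6.5% | 5% |

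With persistent closure the correlation is √[p15(1 − p30) / (p30(1 − p15))]. For closure of 50% then 80% this is √(0.10/0.40) = 0.50, so 9.1%. For 70% then 80% it is √(0.14/0.24) = 0.76, so 8.0%. The fewer fistulas that close between visits, the closer the correlation is to 1 and the rate to 5%.

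**If either visit counts: simulation.** No true effect, 63 per arm, uncorrected chi-square at each visit. The last column is day 15 + day 30 − either.

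| Closure day 15 / day 30 | Day 15 alone | Day 30 alone | Either | Both |
|---|---|---|---|---|
| 50% / 90% | 5.8% | 5.1% | 10.3% | 0.6% |
| 50% / 80% | 5.8% | 4.8% | 9.6% | 1.0% |
| 30% / 70% | 5.0% | 5.0% | 9.3% | 0.7% |
| 60% / 80% | 5.6% | 4.8% | 9.1% | 1.4% |
| 70% / 80% | 5.1% | 4.8% | 7.9% | 2.0% |
| 80% / 85% | 4.8% | 4.7% | 7.2% | 2.3% |
| 85% / 87% | 4.7% | 4.8% | 6.5% | 3.0% |

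The value above 9.75% arises because the uncorrected chi-square is slightly too liberal at this sample size for some rates (5.8% for a single visit). That excess does not come from having two visits.

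**If both visits are required: power.** Assume control 30% / 50% and aPDT 50% / 74%. With 63 per arm, power = Φ{[d − 1.96√(2p̄(1 − p̄)/n)] / √([p1(1 − p1) + p2(1 − p2)]/n)}.

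- Day 30: d = 0.24, p̄ = 0.62, giving 80% (81% by simulation).
- Day 15: d = 0.20, p̄ = 0.40. The numerator is 0.20 − 1.96 × 0.0873 = 0.029 and the denominator 0.0854, so Φ(0.34) ≈ 63% (65% by simulation).

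Power for both cannot exceed the smaller of the two. Simulation gives 60% in this example, and about 58% to 60% over the examples tried.

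**One ordered test.** Scoring closed by day 15, closed by day 30 and not closed, and comparing mean scores once at 5%, gives about 81% power in the same example and about 81% to 83% over the examples tried.

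**The case against.** A reader might infer that the trial tests fistula resolution twice at 5% and so has a false-positive rate of 8% to 10%. The documents do not support that as fact. No section says that each visit is tested separately at 5% or that a result at either visit is enough, and under a both-visits rule the rate is below 5%. Nor is 8% a floor: it needs a correlation between visits of no more than about 0.76, and patterns with few closures between visits give 6.5% to 7.9%. The power loss is equally conditional, because no effect size is stated and the 80% cannot be assigned to either visit.

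It can also be said that rules for combining tests and sharing alpha usually sit in a statistical analysis plan, which is not shown. That is fair for the mechanics of adjustment. It does not cover the time point, which is part of the definition of a primary outcome. The article states that outcome in full more than once and gives two visits each time. This is an outcome fixed badly, not a detail left out for brevity.

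Finally, nothing in the protocol favours day 30 over day 15. That stands, and the choice is for the investigators.

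**Conclusion.** The point holds in conditional form. The primary outcome has two visits and no deciding rule, against one 5% level and one 80% power figure.

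- **Either visit sufficient:** false-positive rate about 6.5% to 10% over the closure patterns tried, approaching 5% as the visits coincide.
- **Both visits required:** false-positive rate about 3% or less in the patterns tried, with power about 58% to 60% where day 30 alone has about 80%.

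These sizes rest on 63 evaluable teeth per arm, closure that persists, and assumed closure rates. That no decisive visit is named rests on no assumption.

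Moving the radiographic item to secondary would not cure this, since the two fistula visits remain. If it stays primary at both visits, there are four tests: 1 − 0.95⁴ = 18.5% if they were independent and any one sufficed. That is a reference value, not an estimate for this trial.

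**What to change.** Amend the Abstract (Methods), the hypothesis paragraph of the Introduction, and Primary outcomes, in one of two ways:

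1. **One primary time point.** For example: fistula resolved at day 30 (yes/no), chi-square, two-sided 5%, with the visit for the investigators to confirm. Make the other visit secondary, and test it confirmatorily only if the primary result is significant.
2. **One ordered test.** If speed of closure should count, pre-name a single two-sided 5% test of the ordered result: closed by day 15, closed by day 30, not closed. It uses both visits, with power similar to day 30 alone in the assumed examples.

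State in the Sample size and Statistical analysis sections that the 5% and 80% refer to that test. Reconcile the radiographic item, primary in one section and secondary in the Abstract, so that the 5% holds overall.

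The cost is a few sentences. Recruitment starts only after the protocol is accepted for publication, and no extra visits or teeth are needed. The downside of option 1 is that a difference seen only at the non-primary visit cannot by itself make the trial positive. Splitting alpha to 2.5% per visit would also work but costs more: for an assumed 70% against 90%, power with 63 per arm falls from 81% to 72%, and the evaluable number needed rises from 62 to 75 per group.

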### Secondary outcomes

• Comparison of Apical Radiolucency: The secondary outcome will involve comparing the apical radiolucency in periapical radiographs of teeth with healed fistulas. This will be assessed before the intervention and at 15 and 30 days post-treatment, focusing on changes in the radiographic appearance of periapical lesions [13].

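### The Abstract has one primary outcome and the Outcome variables section has two; neither names a deciding visit, and the sample size is tied to no outcome or visit.

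*Protocol article*

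**What the plan says.** **Abstract, Methods.** One primary outcome: "The primary outcome is fistula resolution, assessed clinically at 15 and 30 days post-treatment". Radiolucency is secondary, with no restriction on which teeth: "The secondary outcome is the comparison of apical radiolucency from periapical radiographs to evaluate healing and reduction of periapical pathology".

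**Introduction, last paragraph.** The evaluation is said to centre on both fistula resolution and radiographic indicators at days 15 and 30, with neither ranked above the other.

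**Outcome variables, Primary outcomes.** Two items. The first is "The primary outcome will be the resolution of the fistula, assessed at 15- and 30-days post-treatment", and on its assessment: "This will be evaluated based on clinical examination and radiographic evidence". The second is "Radiographic Improvement: The improvement in radiographic signs of apical periodontitis will be assessed at 15- and 30-days post-treatment", with change in periapical radiolucency as its focus.

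**Outcome variables, Secondary outcomes.** "The secondary outcome will involve comparing the apical radiolucency in periapical radiographs of teeth with healed fistulas", compared before the intervention and at both visits.

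**Sample size calculation.** A chi-square homogeneity test is used. "A type I error rate of 5% and a statistical power of 80% were specified", giving 70 (per group, according to the Abstract) after a 10% allowance for loss, and "a significance level of 5% will be employed" in the analysis. No outcome, visit or effect size is given.

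**Statistical analysis.** Tests are listed by type. No visit is singled out.

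**The concern.** The choice of primary endpoint belongs in the protocol, and here it is stated twice in ways that disagree. Radiolucency is secondary in the Abstract and primary in the body. Fistula resolution is a clinical judgement in the Abstract and a clinical and radiographic one in the body. In both places there are two visits and no indication of which one counts.

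The confirmatory claim is at stake. If the results differ by outcome or visit, more than one choice of headline result could be defended afterwards by citing the published protocol. The 5% and 80% in the sample size section describe one test, and the article does not say which.

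**Working it through.** **1. The texts side by side**

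| Place | Fistula resolution | Radiolucency | Deciding visit |
|---|---|---|---|
| Abstract | Primary, clinical | Secondary, no restriction | Not named (15 and 30 days) |
| Introduction | In focus | In focus | Not named (15 and 30 days) |
| Primary outcomes | Primary, clinical and radiographic | Primary | Not named (15 and 30 days) |
| Secondary outcomes | Defines the subset | Secondary, healed fistulas only | Not named (15 and 30 days) |
| Sample size | Not mentioned | Not mentioned | Not mentioned |

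The Abstract implies 1 × 2 = 2 primary comparisons and the body 2 × 2 = 4. Both counts are inferences from outcomes times visits; the article states neither.

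**2. The plan's own figure**

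With no effect size stated, 70 per group cannot be reproduced from the article's inputs. Solving backwards for a 1-df chi-square test, power = P(noncentral χ² with λ = N·w² exceeds the critical value):
- w = 0.25 needs N = 126. Then λ = 126 × 0.0625 = 7.875, power is 80.1%, and 126 / 0.9 = 140, or 70 per group.
- w = 0.20 needs 197, or 219 with loss. w = 0.30 needs 88, or 98 with loss.

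The figure therefore fits one test at w = 0.25. That value is an assumption of this check.

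**3. If any one significant result were enough (each at 5%)**

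Independent tests: 1 − 0.95⁴ = 18.5% for four, and 1 − 0.95² = 9.75% for two. With a common correlation between normal test statistics (simulated, 400,000 draws):

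| Assumed correlation | Four comparisons | Two comparisons |
|---|---|---|
| 0.3 | 17.4% | 9.6% |
| 0.5 | 15.7% | 9.1% |
| 0.7 | 12.9% | 8.3% |
| 0.9 | 9.4% | 7.0% |

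The article gives no correlations. The same tooth seen 15 days apart could well lie towards the high end.

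**4. If all four had to succeed**

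Type I error is not inflated. With 80% power for each, joint power is 0.8⁴ = 41% if independent, and about 50%, 56%, 62% and 70% at correlations 0.3, 0.5, 0.7 and 0.9.

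**5. If all four were kept and corrected by Bonferroni**

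Each test is at 0.05 / 4 = 0.0125. Under the assumed w = 0.25 with 126 evaluable teeth, power is 62% per test. Restoring 80% needs 179 evaluable teeth: 179 / 0.9 = 198.9, so 200 enrolled in equal groups.

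**6. One primary outcome at one visit**

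Under the same assumption: alpha 5%, power 80.1%, 140 teeth, unchanged.

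**The case against.** Four objections have weight.

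- **No success rule is stated.** A reader might infer that a win on any of four results counts, and so that the true type I error is 18.5%. The article does not say this. Any, all or an ordered sequence remain open, and the first primary item uses the singular for fistula resolution, which agrees with the Abstract on the lead endpoint. The error figures are therefore conditional.
- **Multiplicity may be handled in an analysis plan that is not shown.** Silence on correction is not a defect in a condensed article, so the point does not rest on it. An analysis plan would not, however, make the Abstract and the outcome section agree.
- **The body does not list one identical outcome twice.** It is tempting to say that radiolucency is both primary and secondary there. The secondary version covers only teeth with healed fistulas, a subset formed after randomisation. The clear conflict over its status is between the Abstract and the Primary outcomes list.
- **The two definitions of resolution need not give opposite results.** A reader might infer that a closed fistula with persisting radiolucency is a success under one text and a failure under the other. Radiographic evidence is left undefined, radiolucency is a separate item, and fistulography confirms the fistula at entry, so imaging of the tract may be meant. The difference in wording stands; the reversal is only one possible reading.

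The Abstract is also not clean, since its two visits already imply two comparisons.

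**Conclusion.** The contradiction stands: the article disagrees with itself on whether radiographic improvement is primary and on how fistula resolution is judged, and it names no deciding visit. The sample size is attached to no endpoint.

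Its size depends on a rule that the article does not give. On an any-of rule at 5% each, familywise error is about 9% to 18.5% for the body's four comparisons and about 7% to 9.75% for the Abstract's two, over assumed correlations from 0.9 down to 0. On an all-of rule the loss is in joint power: 80% becomes about 70% to 41% over the same range. Either rule applied to the four comparisons departs from a design described by a single 5% and 80%.

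The documents do not support saying that the trial has 62% power. That figure needs both a Bonferroni correction that nobody has specified and the back-solved w = 0.25.

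**What to change.** Make the Abstract, the last paragraph of the Introduction, Primary outcomes and Secondary outcomes agree on:

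1. One primary outcome, fistula resolution, with one stated definition of how it is assessed. If radiographs contribute, say what is read on them and how it combines with the examination.
2. One named visit, for example day 30, tested at 5%. The article does not rank the visits, so the choice is the sponsor's.
3. Fistula resolution at the other visit and radiolucency at both visits as secondary, with radiolucency compared in all randomised teeth. Alternatively, test fistula resolution at the second visit only if the first is significant, which keeps the overall 5%.
4. A sentence in Sample size calculation saying that the calculation refers to that outcome at that visit.

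**Cost.** Radiographic improvement loses its primary status. The sample size stays at 140 teeth and the stated 5% and 80% then describe a single identified test. The article says that recruitment follows acceptance for publication, so enrolment may already have begun. In that case this should be a dated amendment made before any unblinded results are seen.
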